Asthma-Related Emergency Department Visits: Improvements in asthma control can decrease future use asthma-related emergency room visits, so we will measure asthma-related emergency department visits 6,100,101. Claims data are valid measures, and superior to other means, such as self-report, for measuring asthma-related emergency department visits. 102,103. Highmark will send us claims data, at the end of the study, which will identify asthma-related emergency department claims. This is data that is already being analyzed by Highmark, in ways that are standardized by the National Committee for Quality Assurance (NCQA), for reporting the quality of care delivered to patients with asthma 7. In the NCQA reporting, asthma-related emergency department visits are one way to identify patients with persistent asthma 7. We will take advantage of that reporting mechanism in the current study.

Asthma Control and Quality of Life: We will use questions about asthma control and quality of life from the National Asthma Survey, from the CDC and published by Halterman and colleagues (Halterman, Aligne et al. 2000). The instrument identifies several aspects of asthma control and how it impacts quality of life, including days with symptoms, days symptom-free, emergency room visits, urgent doctor visits, asthma attacks, severity of asthma attacks and the degree to which asthma impairs function. It is not clear how many of these questions are validated, but they are used as outcome studies in a great number of asthma clinical trials and have strong face validity and national norms is helpful. Drs. [name], [name] and [name] are working on the adult version of the Halterman paper, using the data from the NAS.

**Mediating Variables:** For our purposes, mediating variables are those that the intervention will attempt to modify in order to bring about a change in asthma control and quality of care for asthma. We will examine variables that have been associated with asthma control and quality of care for asthma and those that have been targeted by the intervention and therefore may mediate the effect of the intervention on the above outcome variables. We hypothesize that each of these variables will mediate the effect of the intervention.

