Intervention fidelity: Use of interactive website before asthma care provider visits. Use of the interactive website will be tracked passively. Each login by study subjects will be recorded, as will the duration of each login, the number of pages viewed, any data entered and the number of times that subjects received the computer-tailored feedback. The active part of the intervention is felt to be the computer-tailored feedback, so this measure will represent the “dose” of the intervention. Dose will be measured as a proportion of asthma provider visits before which the website was used, expressed as a percentage. The number of visits with an asthma care provider will be obtained from chart review, and will be the denominator for this measure. The number of visits that subjects used the website within two weeks prior to these visits will be the numerator for this measure. We consider visits to an asthma care provider to be any visits to the patients’ primary care provider as well as any visits that the patient had with a pulmonary medicine specialist during the study. Upcoming visit dates will be tracked using brief monthly emailed surveys to patients. These surveys will seek to clarify the date(s) of planned visits to asthma care providers, including primary care providers and specialists. All patients who have not used the website within 14 days before their planned visit to an asthma care provider will be sent an automated email reminder, encouraging subjects to use the site or to use a toll-free number to call the study staff if they are having trouble using the website. These email reminders will be repeated 7 days before their next doctor visit and then 3 days before if they have still not used the website. These methods were successful at ensuring a 90% fidelity rate in a pilot RCT of the website 25,27.

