Medication Adherence: The intervention, in some cases, will suggest that patients discuss medication adherence with their provider. This is based on the recommendation (page 336) that “before increasing therapy, however, the clinician should review the patient’s inhaler technique and adherence to therapy” 26. We will measure medication adherence to all asthma controller medications, such as inhaled corticosteroids and long-acting beta-2 agonists, using health care claims for asthma-related medications from Highmark. Health care claims have been shown to be a valid and reliable way to assess medication adherence 109. Our measure of adherence will be the Medication Possession Ratio (MPR), a commonly used measure of adherence, that is highly correlated with other measures of adherence and predictive of asthma exacerbations 111-116. The MPR measures the percentage of doses available to the patient during a specific time period. [name] has experience, through multiple clinical trials for asthma, in measuring adherence to asthma medications and will oversee analysis of medication adherence data 117,118 . Though medication adherence is not a main focus of the intervention, we hypothesize that, by encouraging patients to discuss medication adherence-related issues with their provider, patients in the IC will have higher rates of adherence to their controller medications than subjects in the CC.

**Moderating variables**: For our purposes, moderating variables are those that the intervention will not seek to modify, yet may lead to a differential response to the intervention.

Demographics: Age, gender, race, ethnicity, educational achievement, marital status and household income will be measured, using standardized instruments such as those from the Behavioral Risk Factor Surveillance System 119,120. These variables have been shown to be related to asthma prevalence, asthma quality of care and asthma-related quality of life 121-123. We will assess these variables at baseline and use the data to assess whether demographic variables, such as household income, moderate the effect of the intervention on inhaled corticosteroid use or asthma control.

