Health Literacy: Several studies have identified the link between health literacy and a wide variety of health outcomes 124-127. As the intervention to be tested includes written health-oriented messages, the effects of these messages may be dependent on the individuals’ level of health literacy. To measure health literacy, we will use the Short Form Test of Functional Health Literacy in Adults (s-TOFHLA), which is valid and reliable and is shown to be associated with control of chronic illnesses 124-127. The abbreviated form of the s-TOFHLA is a 36-item timed reading comprehension test with multiple choice responses, and contains two health passages. The test is scored on a scale from 0 to 36. Though we will make sure that all feedback is written at not more than the 6th grade reading level, we hypothesize that the effect of the intervention will be greater among patients with higher levels of health literacy.

Health-related Internet use: We will measure subjects’ use of the Internet for health-related activities, using a survey instrument from the Pew Internet and American Life Project 86,87,128,129. The instrument measures the use of the Internet for a variety of health-related activities (e.g., looking for information about medications). These survey questions will be asked at baseline and at 12 months. As each recommendation in the computer-tailored feedback includes a link to another reputable website with information on the topic, we hypothesize that the effect of the intervention will be greater among patients who have the greatest increases in using the Internet for health-related information.

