Analyses of mediating and moderating processes: The analytic procedures outlined provide a convenient way of identifying effect modifiers and confounders, while modeling the underlying relationship of interest. As noted in the analytic plan for the primary outcome, the analysis of moderators will be undertaken by creating interaction terms between treatment and covariates of interest, such as asthma-related quality of life 139, health literacy and socio-demographic characteristics. We will also examine the effects of treatment fidelity and intervention dosage (e.g. number of visits to web site, total time spent on web site) as potential moderators of intervention efficacy. Mediational analyses will be conducted in the form proposed by Baron and Kenny 140. Briefly, this entails four steps in which it is demonstrated that there is: a) a significant association between the independent variable and the dependent variable; b) a significant association between the independent variable and the mediators; c) a significant association between the mediator and outcome; and d) a meditational effect is argued to occur when a significant decrease in the relation between the independent (e.g. treatment) and dependent (e.g. asthma control) variables upon the forced entry of the proposed mediators into the model at the final step. We will examine each mediator separately, as joint estimation makes estimation and interpretation of the effect of each potentially mediating variable problematic. Data for these analyses will be obtained from online surveys, date stamps from the interactive website and from the timing of physician visits from chart reviews. For example, we can test whether use of the interactive website influences use of other asthma controller medications (e.g., salmeterol). However, we will also explore various temporal combinations between the exogenous (treatment), endogenous mediators (asthma specialist visits) and outcomes and we will pay particular attention to the temporal ordering of key events and measurement periods.

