Ancillary analyses: We plan a detailed tracking and analysis of the delivery and receipt of the intervention components in both the IC and CC conditions. Intervention components will be collected and analyzed using an intervention checklist administered to the subject after the first physician visit, as well as passive monitoring of website usage for all subjects. An implementation index will be calculated for all subjects based on which intervention components each subject was exposed to and for what duration/intensity. This continuous measure will be utilized as a covariate in outcome analyses. Further, we plan to explore the receipt of each treatment component and identify subject characteristics (e.g. age, gender) that are associated with receipt/utilization of a given component. This analytic strategy is particularly useful for gauging utilization of the website. First, we will use descriptive methods to examine total time spent on the website, number of pages viewed and number of times the computer tailored feedback was viewed, all of which can be correlated in relation to the timing of doctor visits, as well as asthma control. Next, we will examine website usage as an outcome variable to characterize which types of patients are more likely to utilize the website. Finally, we plan to examine utilization of the website as predictor of the main study outcomes. These analyses will also be important to provide: a) feedback for website design and management; b) internal validity checks on utilization, which represents dosage and exposure to the intervention; and c) a computation of the effect of dosage, which will be used as a covariate in the prediction of outcomes on the hypothesis that greater utilization of the internet will increase the likelihood of positive outcomes in key intervention indicators, such as use of asthma controller medications. These analyses will permit conclusions regarding the degree to which patient characteristics influence utilization of the website as well as whether the time spent viewing and content of pages viewed influences study outcomes.

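### Exposure measured after randomisation (implementation index, website dosage, 12-month rise in Internet use) is planned as a covariate or moderator, and no text keeps it out of the models that estimate the arm effect

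*Protocol*

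**What the plan says.** **Covariate.** Section 7, Ancillary analyses, defines the index: "An implementation index will be calculated for all subjects based on which intervention components each subject was exposed to and for what duration/intensity". Its use follows: "This continuous measure will be utilized as a covariate in outcome analyses". Later in the same paragraph the protocol plans "a computation of the effect of dosage, which will be used as a covariate in the prediction of outcomes". Neither sentence says which outcome models are meant.

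**Moderator.** Section 7, Analyses of mediating and moderating processes, says: "We will also examine the effects of treatment fidelity and intervention dosage", as potential moderators of efficacy. The examples given are the count of site visits and the time spent on the site.

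**Mediator.** Section 6 places intervention fidelity under Mediating Variables, introduced by "We hypothesize that each of these variables will mediate the effect of the intervention". It defines the measure there: "Dose will be measured as a proportion of asthma provider visits before which the website was used, expressed as a percentage".

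**Internet use.** Section 6 lists health-related Internet use, asked at baseline and 12 months, among the moderators. The hypothesis is that "the effect of the intervention will be greater among patients who have the greatest increases in using the Internet" for health information, on the reasoning that each feedback item links to another website. The same section has already said that "moderating variables are those that the intervention will not seek to modify".

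**Primary analysis.** Section 7 sets an intention-to-treat logistic regression of control at 12 months, performed first and tested through the treatment main effect. The covariates named for it are the strata and possible baseline confounders.

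**The concern.** A covariate fixed before randomisation leaves the arm comparison intact. One that arises afterwards may not. If arm affects the index and the index affects outcome, adjustment removes part of the effect the trial is meant to measure. If arm and patient motivation both drive the index, and motivation also predicts asthma control, adjustment compares unlike patients and can create an arm difference where none exists. A treatment-by-dose interaction has a related weakness: it contrasts patients who chose how much to use the site, and a given level of use may mean different things in the two modules.

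The protocol gives the same exposure three roles (mediator, moderator, covariate), which call for different models and different readings. The Internet-use moderator is complete only when the outcome is measured, and the feedback links can change it. Readers of the ancillary results could meet an adjusted arm effect, or a dose-response, with nothing in the text to say it is not a randomised comparison.

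**Working it through.** **1. The protocol's own figure.** Inputs from section 7: 55% v 70%, two-sided alpha 0.05, power 80%, 20% loss. Equal allocation is assumed because no ratio is stated. With pooled variance and no continuity correction,

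n = [1.960·√(2·0.625·0.375) + 0.842·√(0.55·0.45 + 0.70·0.30)]² / 0.15² = (1.342 + 0.569)² / 0.0225 ≈ 162.3, so 163 per arm and 326 in total. Then 326/0.80 = 407.5, so 408.

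The stated 408 and 326 are reproduced, and power at 163 per arm is 0.802. The calculation concerns the unadjusted comparison, so this point does not alter the sample size.

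**2. What adjustment does.** To a first approximation,

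adjusted log OR ≈ unadjusted log OR − (difference in mean use between arms) × (slope of outcome on use within arms).

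So the distortion needs both a difference in use by arm and a relation of use to outcome.

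**3. Illustration.** The use levels and effect strengths are assumptions, since the protocol gives none. There are 163 per arm, mean use is 60% in the asthma arm (IC), and the benefit works wholly through IC exposure. The design log OR is ln(2.333/1.222) = 0.647, so the slope in IC is 0.647/0.60 = 1.08 per unit of use, and zero in the control arm (CC).

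- Equal use: the difference is 0, so there is no shift.
- CC 50%: the pooled slope is about 1.08/2 = 0.54 and the shift 0.10 × 0.54 = 0.054. From a simulated unadjusted OR of 1.89, exp(0.637 − 0.054) = 1.79.
- CC zero: only IC varies, so the slope is 1.08 and the shift 0.60 × 1.08 ≈ 0.65. The adjusted log OR is about 0.

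Simulated trials agree:

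| Mean index, CC v IC | Adjusted arm OR | Rejection rate |
|---|---|---|
| 60% v 60% | 1.90 (unadjusted 1.89) | 78% (unadjusted 78%) |
| 50% v 60% | 1.79 | 69% |
| 0 v 60% (only asthma components counted) | 1.00 | 4% |

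With equal use, there is still no material change when engagement also predicts outcome: OR 1.87 unadjusted, 1.91 adjusted.

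**4. No treatment effect, engagement predicts outcome.** Assume a log OR of 0.5 per SD of use and a within-arm SD of 0.19. With use of 50% v 60%, the shift is (0.10/0.19) × 0.5 ≈ 0.26, an adjusted OR near exp(−0.26) = 0.77. The simulated false rejection rate is 19%. If the arms differ by a full SD of the index, the approximation gives exp(−0.5) = 0.61. The simulation gave 0.60, with false rejection 50% against 4% unadjusted.

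**5. Moderator test.** With no treatment effect, and an index that reflects engagement in IC only (same 0.5 per SD), the treatment-by-index interaction was falsely significant in 58% of simulated trials.

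**6. Internet use.** No arithmetic applies. The hypothesis concerns an increase completed at 12 months, and its stated reason is that the feedback sends patients to other sites. The variable is therefore one the intervention can move, which is what the moderator definition excludes.

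**The case against.** Three points on the other side carry weight.

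**The arms are matched for contact.** Section 3 treats control subjects identically apart from content, section 5 gives both arms the same schedule of use, and the index is computed for everyone. If it measures generic use and use is equal, adjustment does no harm. A reader might infer that adjusting for the index must erase the treatment effect. The documents do not support that: the collapse to an OR of 1.0 requires an index that is zero in the control arm. What remains is that the content of the index is undefined and equal use is not assured. Section 3 has the asthma feedback suggest earlier visits to some patients, and the site is to be used before visits.

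**The randomised primary result stands apart.** A reader might infer that the primary analysis is contaminated. The text does not say so. That analysis is intention to treat, comes first, tests the treatment main effect, and names only strata and baseline confounders. The covariate sentences sit under a heading for ancillary work, and the secondary analyses follow the primary plan. This limits the point, but the phrase on outcome analyses has no boundary, and no sentence marks these estimates as non-randomised.

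**Some models must contain these variables.** The mediation steps in section 7 enter a mediator beside treatment by design. A ban covering every model with an arm term would forbid them, so the remedy must except them.

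**Conclusion.** The point holds, and it should be corrected. The protocol prescribes post-randomisation exposure as a covariate without saying where, tests dosage as a moderator after classing it as a mediator, and uses a 12-month change as a moderator against its own definition. The consequences fall on the ancillary and moderator analyses, and reach the secondary models only on a broad reading.

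No single figure describes the size. Under the stated assumptions, the adjusted arm OR runs from no distortion (equal use), through about 1.8 with 69% rejection (50% v 60%), to about 1.0 with 4% rejection (asthma components only). Where use differs by arm and engagement predicts control, a false arm effect can appear, with 19% rejection in the modest case. There is no such bias if the index is unrelated to arm, or unrelated to outcome both directly and through engagement. The direction of the problem is firm; its magnitude in this trial cannot be known from the protocol.

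**What to change.** 1. State in section 7 that the implementation index, dosage and follow-up Internet use will not be covariates or treatment-interaction terms in any primary or secondary model used to estimate or test the randomised arm effect. Except the planned mediation models explicitly.
2. Report dose-outcome relations as associations within the asthma-module arm, labelled non-randomised. A complier-average estimate with randomisation as the instrument is an option, provided its assumptions are stated.
3. Use baseline Internet use, already collected, as the moderator. Treat its change to 12 months as a candidate mediator.
4. Give website dose one role, consistent between sections 6 and 7, and say what the index counts in each arm.

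The cost is revised wording, a different exploratory analysis, and loss of the dose-by-treatment moderator test. No new data are needed, and the sample size stays at 408.

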**8. Risks and Discomforts**

The main discomforts or risks in this study is loss of confidentiality, psychological stress induced by the questions in the surveys, and receiving incorrect recommendations for asthma care. These risks are rare.

### 9. Benefits

Participants may experience better communication with their primary care providers and improved asthma and preventive care. This project may also provide a new way to foster doctor-patient communication and improve the quality of asthma and preventive care.

### Safeguards and Confidentiality

Confidentiality will be maintained by numerically coding all data, by disguising identifying information and by keeping all data in locked file drawers. All information obtained from subjects will be accessible only to research staff. In addition, the website currently uses the following methods to assure the confidentiality and security of patient data: The website and data collected are stored on PHS servers. Data transmissions over the network will be encrypted using a 128-bit Secure Sockets Layer (SSL) encryption standard, for which PHS has its own security certificate. The SSL protocol provides data security layered between application protocols (such as Hypertext Transfer Protocol (HTTP) and Transfer Control Protocol/Internet Protocol (TCP/IP). This security protocol provides data encryption, server authentication, message integrity, and client authentication for a TCP/IP connection. Computer network security is maintained through network hardware, user authentication, and user roles within the WebAsthma application and its corresponding database. All computers connect through an Internet firewall that prevents unauthorized users from gaining access to the internal network structure. The firewall protects the computer network, and PHS staff members are experienced with the requirements for database access through an active firewall. The local firewall is monitored continuously and equipment logs are reviewed daily for abnormalities or security issues. The database roles facilitate or restrict access to specific website functionality. The database application meets the security requirements of HIPAA.

